### Data collection

At baseline and 3, 6, 9 and 12 months, respectively, from the participant’s inclusion in the study, an email containing a link to an online questionnaire will be sent to the participants. All collected data will be self-reports, including a 30 s chair stand self-test (30CST). In the absence of completed questionnaires, a reminding email will be sent out after 1 week. If further absence, another email will be sent after an additional week. This reminder will also include a question if they want to withdraw from the study. Data registered in the exercise diary of the application are collected continuously. In the same monthly email as the educational videos, all participants will receive a request to report any falls during the past month by answering a short web-based questionnaire. In the absence of a completed questionnaire, one reminder will be sent after 1 week. All data retrieved from questionnaires, as well as application data, will be coded and reported on a group level.

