### Outcomes

#### Primary outcome

The primary and secondary outcomes, and time points of distribution are presented in table 2. The primary outcome measure will be the rate of falls (fall per person/year) during the 12 months of the intervention. To register falls, a link to a self-report online questionnaire will be sent monthly by email. To be able to report correctly the coming month, participants are asked to make notes of falls in a calendar, preferably the day the fall has occurred. They will be provided with a printable calendar in the email sent out after allocation, but they can also use their own. If a fall is reported, additional questions will be asked about the cause of the fall, potential injuries sustained, need for medical attention and hospitalisation. The number of persons falling during 12 months will be analysed based on the same data as a secondary outcome.

**Table 2 T2:** List of primary and secondary outcome measures

Outcome measures	BA	C	M	3 months	6 months	9 months	12 months
Fall rate† (fall per person/year)			X				
Number of fallers‡ (n)			X				
Number of falls during exercise with Safe Step§ (n)			X				
Fall-related injuries§ (yes/no, need of medical attention, type of injury)			X				
Hospitalisation due to falls§ (yes/no and number of days)			X				
Reach§ (self-reported sociodemographic parameters such as age, sex, years of education, use of smartphone and tablet, number of cohabitants and self-reported health and diagnosis)	X						
Self-administered 30 s chair stand test¶	X			X	X	X	X
The Borg Scale of Perceived Exertion during 30 s chair stand test** (numeric scale, score 6–20)	X			X	X	X	X
Self-rated balance**, ‘How do you perceive your balance?’ (5-level ordinal scale)	X			X	X	X	X
Self-rated leg strength**, ‘How do you perceive your leg muscle strength?’ (5-level ordinal scale)	X			X	X	X	X
Fear of falling¶ (Falls Efficacy Scale-International)	X			X	X	X	X
Health-related quality of life¶ (EQ-5D-5L)	X			X	X	X	X
Experienced positive effects of the exercise intervention§ (nominal scale, optional text field)	X*			X*	X*	X*	X*
Experienced negative effects of the exercise intervention§ (nominal scale, optional text field)	X*			X*	X*	X*	X*
Exercise adherence throughout the intervention reported through an integrated exercise diary in the Safe Step application§,¶		X*					
Exercise adherence, self-reported min/week§				X*	X*	X*	X*
Use and perceived usefulness of educational videos** (4-level ordinal scale)				X	X	X	X

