At the end of the 12-month intervention, the participants in both groups will be asked if they have started to do any other exercise activities or programmes during the intervention period. In addition, self-rated improvements in balance and leg strength over the whole course of the intervention will be measured through single-item questions. Both groups will also be asked to report if they have had any extra cost related to the intervention during the intervention period (eg, for internet access or equipment) to inform the cost-effectiveness analysis. Drop-outs and withdrawals from the study will be registered throughout the 12-month intervention. Withdrawals will be defined as those who have formally discontinued the study by filling in the withdraw questionnaire. Participants that consistently discontinue to answer the questionnaires will be defined as drop-outs.

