### Planned statistical analyses

Analyses will be performed according to the intention-to-treat principle. Thus, all available data for each randomised participant will be analysed according to original allocation and regardless of level of participation. The primary outcome, that is, the number of falls per person year, will be analysed using negative binomial regression to account for an expected overdispersion with respect to Poisson distribution.^46^ The fall rate ratio of the two groups will be estimated with a 95% CI and presented with a p value while adjusting for the prognostic baseline covariates of age and sex for the purpose of increasing precision in estimates and statistical power. In addition, unadjusted results will be presented in accordance with recommendations from the CONSORT 2010 statement.^33^

For secondary outcomes on ordinal variables measured quarterly, analysis will be performed using cumulative link mixed models with logit link function and group, time point and group*timepoint interaction as fixed factors and participant as a random factor. In continuously scored secondary variables measured quarterly, general mixed linear models will be used to assess the group difference. Logistic regression models will be used to compare groups on dichotomous outcome measures.

Effects on falls, attrition and self-reported effects on balance and strength will be studied in subgroup analyses in relation to sex, different age groups, reported health status, physical activity and use of smartphones and tablets. Further subgroup analysis will examine exercise adherence in the exercise group as well as the dose–response relationships (min/week). Descriptive statistics will be provided to reveal the sociodemographic distribution in the sample in comparison to the population and geographical distribution in urban and rural areas.

Multiple imputation will be performed on variables containing data considered to be missing at random if proportions of missing data does not exceed 40%, as suggested in literature.^47^ In addition, analysis on original unimputed data will be presented as supplement. All statistical tests will be two sided with a significance level of 0.05.

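### A missed monthly fall report, the only source of the primary outcome, gets one reminder; a missed quarterly questionnaire gets two, and the second invites withdrawal from the whole study

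*Protocol article*

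**What the plan says.** The Data collection section of the protocol article sets two follow-up rules.

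- **Quarterly questionnaires (3, 6, 9 and 12 months; the baseline form has the same rule).** "In the absence of completed questionnaires, a reminding email will be sent out after 1 week". Then: "If further absence, another email will be sent after an additional week". Of that second email the section adds: "This reminder will also include a question if they want to withdraw from the study".
- **Monthly fall report.** "In the absence of a completed questionnaire, one reminder will be sent after 1 week". No further step is stated.

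The Primary outcome section ties the endpoint to the monthly form: "The primary outcome measure will be the rate of falls (fall per person/year) during the 12 months of the intervention", and "To register falls, a link to a self-report online questionnaire will be sent monthly by email". In Table 2 the fall rate is marked only in the monthly column, and the outcomes in the quarterly columns are all secondary.

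The Secondary outcomes section defines formal exit: "Withdrawals will be defined as those who have formally discontinued the study by filling in the withdraw questionnaire". It describes no intermediate status in which someone stops the quarterly forms but goes on reporting falls.

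**The concern.** Fall counts and the person-time behind them come from one short monthly form. That form gets the weaker chase when it is missed. The stronger chase belongs to the longer quarterly form, which includes a chair stand self-test and several scales, and its last step asks about leaving the study altogether. Someone who has merely not completed a secondary-outcome form is thus asked a question whose affirmative answer, as described, would also end their fall reporting.

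At stake is the completeness of the primary outcome. The Sample size section and the Discussion anticipate 50% attrition, and the article's list of strengths and limitations names a risk that losses will differ between groups. Only the intervention arm is asked to exercise three times a week, keep a diary and answer extra items, so uneven loss is plausible. Reports that were never collected cannot be recovered by any analysis method, so this belongs to data collection and not to a later analysis plan.

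**Working it through.** **1. The two rules side by side** (Data collection; Table 2)

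| | Monthly fall report | Quarterly questionnaire |
|---|---|---|
| Outcomes carried | Primary (fall rate) and fall-derived secondary outcomes | Secondary only |
| Reminders per missed form | 1 (at 1 week) | 2 (at 1 and 2 weeks) |
| Withdrawal question in a reminder | None stated | Yes, in the second, about the whole study |
| Fall-reports-only option | None described | None described |
| Maximum emails over follow-up | 12 × (1 request + 1 reminder) = 24 | 4 × (1 request + 2 reminders) = 12 |

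Per missed form, fall reports get half the reminders. In total emails they get twice as many, because they are requested every month.

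**2. The plan's own sample size, to set a scale**

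Inputs from Sample size and Planned statistical analyses: control rate 1 per person-year, 20% reduction (0.8), overdispersion 1.2, two-sided 5%, 80% power, 420 per group, at least 1400 in total. Here (1.960 + 0.842)² = 7.849 and (ln 0.8)² = 0.0498.

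- With 1.2 as a multiplier of the Poisson variance: n = 1.2 × 7.849 × (1/1.0 + 1/0.8) / 0.0498 = 426 per group. This reproduces 420 to within 2%.
- With 1.2 as the negative binomial dispersion k: n = 7.849 × (1/1.0 + 1/0.8 + 2 × 1.2) / 0.0498 = 733 per group. This does not reproduce 420.
- 840/1400 = 0.60, so 1400 corresponds to about 60% of planned person-time being observed.

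Which reading of 1.2 was intended is a separate question. Both are carried below so that the illustration does not depend on it.

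**3. Illustration: loss of fall reports cut from 50% to 40%**

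Both percentages are used as assumptions. The 50% is the protocol's attrition figure; the 40% is hypothetical. There are 700 per arm. Drop-outs contribute either 0.2 years each or exit uniformly over the year (0.5 years on average).

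Power = Φ(0.2231/SE − 1.960), where

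- variance multiplier: SE² = 1.2 × (1/t + 1/(0.8t)) / 700, with t the mean observed time;
- k = 1.2: SE² = the sum over arms of 1/(700 × mean information), with information μt/(1 + 1.2μt) per person.

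| Reading of 1.2 | Drop-outs contribute | Power at 50% loss | Power at 40% loss | Gain (points) |
|---|---|---|---|---|
| Variance multiplier | 0.2 y (t = 0.60, then 0.68) | 79.5% | 84.2% | 4.7 |
| Variance multiplier | uniform (t = 0.75, then 0.80) | 87.5% | 89.5% | 2.0 |
| k = 1.2 | 0.2 y | 61.1% | 65.2% | 4.1 |
| k = 1.2 | uniform | 69.3% | 71.2% | 1.9 to 2.0 |

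The gain is about 2 to 5 points under either reading.

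**4. Dilution of the 12-month rate ratio**

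Suppose, as a further assumption, that unobserved intervention-arm time runs at the control rate while observed time has a ratio of 0.80. With a fraction u unobserved, the 12-month ratio is 0.80(1 − u) + u.

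- At 50% loss, u = 0.25 (uniform) to 0.40 (0.2 y), giving 0.85 to 0.88.
- At 40% loss, u = 0.20 to 0.32, giving 0.84 to 0.86.

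The assumed improvement moves the ratio by 0.01 to 0.02. The 0.85 to 0.88 range reflects all unobserved time and cannot be charged to the reminder rule.

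**The case against.** **Total contact.** Fall reporting generates up to 24 emails against 12, and a monthly non-responder hears again with the next request, about three weeks after the reminder. Fewer reminders on a more frequent form is a defensible way to limit burden. This stands as far as it goes: the imbalance is per missed form, not in total contact. But the next request asks about the following month, and the article does not describe a way to complete the earlier one.

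**Stronger readings that the document does not support.** A reader might infer three further things.

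- *That people who stop exercising or skip the long forms cannot report falls.* Data collection sends the monthly request to every participant, with no condition on exercising or on answering quarterly forms. Someone can ignore the quarterly forms and still answer the short one. Only the content of the withdrawal question is at issue.
- *That the withdrawal question contradicts intention-to-treat.* The commitment is that "all available data for each randomised participant will be analysed according to original allocation and regardless of level of participation". Asking whether someone wishes to leave does not breach a promise to analyse what is available.
- *That a missed month is irretrievable.* The article does not say that the link closes or that late entry is refused, and participants are asked to note falls in a calendar.

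**Condensed article.** The wording of the withdrawal questionnaire may be given in a fuller protocol. This is fair, and limits the second half of the point to what is described here. It does not touch the reminder counts, which are stated outright.

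**Size.** The move from 50% to 40% has no support in the document, since no response rate by number of reminders is given. This stands in full.

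**Conclusion.** The point holds in a limited form. By the protocol's stated rules, a missed primary-outcome form is followed up less than a missed secondary-outcome form, and continued silence on the secondary-outcome form triggers a question about leaving the study, with no fall-reports-only choice described. In a trial that expects 50% attrition and fears unequal loss, this is a weakness in retention design. It is not a contradiction, and it does not invalidate the analysis.

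Its size cannot be determined from the document. The 2 to 5 points of power rest on an assumed drop in loss from 50% to 40%, on 700 per arm, and on assumed exposure among drop-outs; they show what better completeness would be worth, not what one more reminder would deliver. That loss is uneven between arms because of these rules is likewise plausible but not shown. The case for change rests on low cost set against the trial's own main declared limitation.

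**What to change.** 1. In Data collection, give the monthly fall report a second automated reminder after a further week, matching the quarterly forms.
2. Word the withdrawal question so that a participant may stop the programme, the quarterly questionnaires or both while still sending the monthly fall report, with full withdrawal as a separate choice. Record which was chosen, and adapt the definition of withdrawal in Secondary outcomes to match.

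Optional: let the next monthly form ask about an unreported earlier month. This is a trade-off, because it brings longer recall into a prospectively recorded outcome. If adopted, flag such entries and repeat the primary analysis without them.

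Cost: one more email to non-responders, small edits to automated emails and one form, and an ethics notification. The sample size does not change.

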### Outcomes

#### Primary outcome

The primary and secondary outcomes, and time points of distribution are presented in table 2. The primary outcome measure will be the rate of falls (fall per person/year) during the 12 months of the intervention. To register falls, a link to a self-report online questionnaire will be sent monthly by email. To be able to report correctly the coming month, participants are asked to make notes of falls in a calendar, preferably the day the fall has occurred. They will be provided with a printable calendar in the email sent out after allocation, but they can also use their own. If a fall is reported, additional questions will be asked about the cause of the fall, potential injuries sustained, need for medical attention and hospitalisation. The number of persons falling during 12 months will be analysed based on the same data as a secondary outcome.

**Table 2 T2:** List of primary and secondary outcome measures

Outcome measures	BA	C	M	3 months	6 months	9 months	12 months
Fall rate† (fall per person/year)			X				
Number of fallers‡ (n)			X				
Number of falls during exercise with Safe Step§ (n)			X				
Fall-related injuries§ (yes/no, need of medical attention, type of injury)			X				
Hospitalisation due to falls§ (yes/no and number of days)			X				
Reach§ (self-reported sociodemographic parameters such as age, sex, years of education, use of smartphone and tablet, number of cohabitants and self-reported health and diagnosis)	X						
Self-administered 30 s chair stand test¶	X			X	X	X	X
The Borg Scale of Perceived Exertion during 30 s chair stand test** (numeric scale, score 6–20)	X			X	X	X	X
Self-rated balance**, ‘How do you perceive your balance?’ (5-level ordinal scale)	X			X	X	X	X
Self-rated leg strength**, ‘How do you perceive your leg muscle strength?’ (5-level ordinal scale)	X			X	X	X	X
Fear of falling¶ (Falls Efficacy Scale-International)	X			X	X	X	X
Health-related quality of life¶ (EQ-5D-5L)	X			X	X	X	X
Experienced positive effects of the exercise intervention§ (nominal scale, optional text field)	X*			X*	X*	X*	X*
Experienced negative effects of the exercise intervention§ (nominal scale, optional text field)	X*			X*	X*	X*	X*
Exercise adherence throughout the intervention reported through an integrated exercise diary in the Safe Step application§,¶		X*					
Exercise adherence, self-reported min/week§				X*	X*	X*	X*
Use and perceived usefulness of educational videos** (4-level ordinal scale)				X	X	X	X
Self-rated improvements in balance††, ‘If you compare with when you started this study a year ago, how would you assess balance today?’ (5-level ordinal scale)							X
Self-rated improvements in leg-strength††, ‘If you compare with when you started this study a year ago, how would you assess the muscle strength in your legs today?’ (5-level ordinal scale)							X
Rate of attrition‡ (n)							X
New exercise routines§ (yes/no, text field to describe the exercise, time since initiation (predefined alternatives), min/week (predefined alternatives))							X
Physical activity¶ (min/week, predefined alternatives)	X						X
Self-reported costs related to the interventions§ (amount and what)							X
Cost effectiveness of the interventions with respect to falls¶							X

*Only administered to the exercise intervention group,

†Negative binomial regression.

‡Logistic regression.

§Descriptive analysis.

¶Linear mixed model.

**Cumulative link mixed model.

††Ordinal logistic regression.

BA, baseline assessment; C, continuously; EQ-5D-5L, European Quality of Life, 5 dimensions; M, monthly administered.

Falls will be defined as an event in which the person comes to rest inadvertently on the ground or floor, regardless of what caused the fall or if an injury was sustained. Our definition is slightly modified and clarified in comparison with a previous consensus statement.^30^ The ProFaNE definition included falls where the person come to rest on an ‘other lower level’, for example, tripping and taking a hold of a dresser.^30^ We exclude ‘lower level’ as our experience from previous studies is that participants seldom perceived such an event as a fall. In accordance with a systematic review,^38^ we clarify that a fall should be reported regardless of cause and we also clarify that unintentionally coming to rest on the floor or ground is a fall regardless of injury. Our definition is printed in the online questionnaire.

#### Secondary outcomes

Sociodemographic parameters, such as age, sex, health, use of smartphones and tablets, and living conditions will be collected at baseline to understand which older adults who are reached through the intervention and to be able to assess predictors of completion.

Self-reported data regarding physical assessments will be collected at baseline, 3 months, 6 months, 9 months and 12 months, respectively. Single-item questions with a 5-graded Likert scale are used to assess self-rated improvements in strength and balance (table 2). A 30 s chair stand test is performed by the participants following instructions in the online questionnaire. The original administration of the test has shown excellent test–retest reliability and criterion validity for assessing functional lower extremity leg strength in older adults,^39^ but studies regarding the psychometric properties of a self-test is lacking. Instructions for the participants to be able to perform the 30CST by themselves at home were developed by the research group. After feedback from an advisory group of older adults, the instructions were slightly revised. When performing the test, the participants are asked to place a chair against the wall and take a seat in the middle of the chair with both feet in full contact with the floor and arms folded across the chest. They are instructed to fully stand up and sit down as many times as possible for 30 s and register the number of full stands. Participants are asked to use the Borg Scale of Perceived Exertion^40^ in combination with the 30CST test to quantify their effort. The perceived exertion is rated on a scale between 6 (none) and 20 (maximal exertion).

The Swedish version of Falls Efficacy Scale-International (FES-I(S))^41^ will be used to measure concerns about falling. FES-I is widely used among older adults and is suitable for use in different populations and in clinical trials.^42^ The FES-I and FES-I (S) have shown excellent internal and test–retest reliability.^41 43^

Health-related quality of life will be included in the secondary outcomes to enable us to conduct economic analysis and will be assessed by the European Quality of Life, 5 dimensions (EQ-5D-5L)^44^ self-report questionnaire. Cost effectiveness will be conducted from a societal perspective at 12 months.

Both groups will also be asked to rate their use and perceived usefulness of the monthly delivered educational videos on 4-level ordinal scales.

Additional questions will be asked to the exercise intervention group regarding adherence, experienced positive effects besides strength and balance, and adverse events. Adherence to exercise will be evaluated by self-report questions at follow-up assessments through predefined alternatives, and will be summarised as exercised min/week. Additionally, adherence to exercise including the proportion meeting at least the predefined minutes of 3×30 min/week, will be collected through an exercise diary integrated within the Safe Step-application.

At self-report assessments at 3, 6, 9 and 12 months after study start, a single-item question with predefined answers will be used to assess experienced positive effects of the exercise intervention besides effects on balance and strength.

Adverse events in form of falls occurring while exercising with the Safe Step application will be monitored monthly. If a participant registers a fall in the monthly questionnaire, there will be a follow-up question of whether the fall occurred while exercising with the Safe Step programme. If so, a member of the research team will contact the participant to ask him or her about the nature of the fall, and if necessary, suggest measures to prevent further falls during exercise. Additional adverse events of taking part in the intervention (eg, muscle strain) will be collected at assessments at 3, 6, 9 and 12 months after study start, and measured through a single-item question: ‘Have you experienced any negative effects of the exercise intervention?’ The participants will be presented with predefined alternatives and an optional text field.

At the end of the 12-month intervention, the participants in both groups will be asked if they have started to do any other exercise activities or programmes during the intervention period. In addition, self-rated improvements in balance and leg strength over the whole course of the intervention will be measured through single-item questions. Both groups will also be asked to report if they have had any extra cost related to the intervention during the intervention period (eg, for internet access or equipment) to inform the cost-effectiveness analysis. Drop-outs and withdrawals from the study will be registered throughout the 12-month intervention. Withdrawals will be defined as those who have formally discontinued the study by filling in the withdraw questionnaire. Participants that consistently discontinue to answer the questionnaires will be defined as drop-outs.

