### Randomisation and blinding

After completed baseline questionnaire, the participants will be randomised in a 1:1 ratio using permuted block randomisation with randomly varied block sizes. A statistician not involved in the study will generate the allocation list using the randomizeR R-package before enrolment.^36^ A computer programme developed in FLOW, Microsoft Office 365-software, will randomise participants according to the allocation list.

After randomisation, the FLOW programme will automatically send emails with follow-up questionnaires as well as the monthly fall reports and educational videos. In order to include participants, monitor data collection and answer emails regarding technical issues, two members of the research group will be able to see the participant’s email addresses and group allocation in the FLOW system and database. However, no personal contact will occur between researchers and participants regarding the results of their outcome assessments.

Analyses of the outcomes regarding falls and physical function will be made by a researcher blinded to group allocation. Participants will not be blinded due to the nature of the intervention.

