Adherence to individual exercise-based fall prevention is often poor over time.^10^ A contributing factor could be a lack of social components and peer support, which has been shown to positively affect attendance and adherence to exercise classes among older adults.^48^ However, preferences are diverse among older adults, and some older adults have stated to prefer home-based exercises.^15^ Due to the nature of this home-based intervention with online recruitment and an intervention period of 1 year, an attrition rate of 50% is anticipated. Still, this study will assess the effectiveness of a self-managed digital exercise programme to prevent falls in real-life settings where the older adults themselves will take the initiative to download and use an application. Hence, the attrition rates will be a valuable contribution in understanding more about older adult’s exercise adherence when exercising with smartphones and tablets in a home-based setting.

Home-based exercise has been shown to be preferred among older adults of advancing age, those with recent falls, and those with lower socioeconomic status.^15^ On one hand, fall prevention interventions delivered by digital technology might create a constraint for older adults who cannot afford digital technology or do not have digital competency. On the other hand, digital technology will present opportunities for older adults that might not have the opportunity or interest in attending community-based programmes or regularly visit healthcare centres. Additionally, in recent years, the use of digital technology such as smartphones and tablets has increased sharply among older adults. In 2019, 67% of the aged Swedish population used the internet on their smartphone, and 40% on their tablet,^49^ and the rapid increase in use is expected to continue. In light of these considerations, it is important to explore reach as suggested in the present study to describe which older adults that are interested in exercising with a digital application with no interaction with a healthcare professional.

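### Non-fall harms of the exercise have no listed collection point for participants who withdraw between quarterly questionnaires, and Table 2 marks the item at a baseline where it cannot be asked

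*Protocol article*

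**What the plan says.** The Secondary outcomes section of the protocol article sets the schedule for harms other than falls: "Additional adverse events of taking part in the intervention (eg, muscle strain) will be collected at assessments at 3, 6, 9 and 12 months". The instrument is one self-report question, "measured through a single-item question: ‘Have you experienced any negative effects of the exercise intervention", with predefined answers and optional free text.

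Table 2 has a matching row, "Experienced negative effects of the exercise intervention§ (nominal scale, optional text field", analysed descriptively. Each mark in that row carries an asterisk, explained in the footnote as "Only administered to the exercise intervention group". There are five marks: baseline, 3, 6, 9 and 12 months. The row for positive effects has the same five.

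Falls during exercise are handled separately: "Adverse events in form of falls occurring while exercising with the Safe Step application will be monitored monthly", with contact from the research team when one is reported. Fall injuries and hospitalisation due to falls are also collected monthly.

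On timing, the Randomisation and blinding section says: "After completed baseline questionnaire, the participants will be randomised in a 1:1 ratio". On leaving the study, Secondary outcomes says: "Withdrawals will be defined as those who have formally discontinued the study by filling in the withdraw questionnaire". People who simply stop answering are classed as drop-outs. The Discussion states that "an attrition rate of 50% is anticipated".

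**The concern.** The schedule has a gap for one group. Someone who has a non-fall harm and formally withdraws before the next quarterly form meets no listed occasion on which that harm is recorded. The gap is longest at the start, because the first quarterly form comes at 3 months and the monthly forms before it concern falls.

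If the harm itself makes people leave, the people missing from the harm item are disproportionately those who were harmed. The descriptive proportion at each quarter then describes those who tolerated the programme well enough to stay. This matters because the Background and Discussion present the programme as a candidate for wide use without contact with health professionals, so its harm estimate will be relied on.

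The baseline mark in Table 2 is a separate and smaller matter. It is a plain contradiction, clerical in itself.

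**Working it through.** **1. Is there a listed collection point for the group in question?**

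| Occasion | What the article lists | Captures a non-fall harm? |
|---|---|---|
| Baseline questionnaire | Table 2 mark, exercise arm only | No: completed before allocation |
| Monthly form | Falls, falls during Safe Step exercise, fall injuries, hospitalisation due to falls | No |
| Quarterly forms, 3 to 12 months | Single item on negative effects | Yes, if returned |
| Withdraw questionnaire | Existence only; items not described | Not stated |

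The Data collection section adds a detail. After an unanswered questionnaire, the second reminder asks whether the participant wants to withdraw. Someone who withdraws in reply to it has not, at that point, completed that form, and so has not answered that quarter's harm item.

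**2. Baseline mark.** Table 2 has four follow-up columns and five marks in the row, so one mark must be baseline. The text lists only the four follow-up times. The baseline questionnaire comes before randomisation, when there is no exercise arm and no exercise to have had effects. The same reasoning applies to the positive-effects row, whose text also lists only 3, 6, 9 and 12 months.

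**3. Size.** The article states no harm rate and no timing of attrition, so there is no figure to reproduce. What follows is an illustration, for the 3-month form only.

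Inputs, all assumed except the 50%:
- *L*, the share of the exercise arm gone before the 3-month form. Two values: 25% (assumed), and 1 − 0.5^(3/12) = 15.9%, which is the stated 50% at 12 months spread at a constant rate (also an assumption).
- *p*, the true risk of a non-fall harm by then: 5%, 10% or 20% (assumed).
- *k*, how many times as likely a harmed person is to leave: 1 to 4 (assumed).

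The probability of leaving among the unharmed is x = L / (pk + 1 − p). The share of harmed people not recorded is kx. The proportion seen among responders is p(1 − kx) / (1 − L).

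Example with L = 25%, p = 10%, k = 2: x = 0.25 / 1.1 = 0.227, kx = 45%, and the observed proportion is 0.10 × 0.545 / 0.75 = 7.3%.

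For p = 10%:

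| k | Observed, L = 25% | Harmed not recorded | Observed, L = 15.9% | Harmed not recorded |
|---|---|---|---|---|
| 1 | 10.0% | 25% | 10.0% | 16% |
| 2 | 7.3% | 45% | 8.5% | 29% |
| 3 | 5.0% | 63% | 7.2% | 40% |
| 4 | 3.1% | 77% | 6.1% | 49% |

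Varying the true risk at k = 2: a true 5% appears as 3.5% (L = 25%) or 4.1% (L = 15.9%), and a true 20% as 15.6% or 17.5%.

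At k = 1 the proportion is unbiased, but the events of those who left are still missing from the count. The calculation treats every early leaver as unrecorded, whether by formal withdrawal or by silence. The withdraw form could recover only the first kind, and the article does not give the split.

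**The case against.** The strongest objection concerns the withdraw questionnaire. Its items are not shown, and an article commonly leaves the content of such a form to the full protocol. It may already ask about negative effects or reasons for leaving. That stands, and the fix is conditional on it. It does not remove the point, because the article does fix the collection schedule for this outcome, in the text and in Table 2, and the withdraw form is not on it.

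A reader might go further and infer that people harmed by the exercise are never asked. The document does not support that:
- Falls during exercise are asked about monthly.
- Someone who stops exercising but stays in the study still receives the item.
- A harm reported on an earlier form is already recorded.
- The question as quoted has no recall limit, so a missed 3-month form can be made good at 6 months.
- The article describes quarterly emails with two reminders, so silent drop-outs are sent the item and do not reply.

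A reader might also infer that reported harm will be too low. That requires leaving to be related to harm. It is plausible for an exercise programme, but the document gives no evidence of it.

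Finally, the outcome is descriptive, the article already names large attrition as a limitation, and the numbers above rest on assumed inputs. All true. These limit the weight of the point but do not close the gap.

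**Conclusion.** The point holds in a limited form. Non-fall negative effects rest on the four quarterly forms, and an exercise-arm participant who has such a harm and formally withdraws before the next form has no listed occasion for recording it. Reported harm will be too low if harm prompts leaving; the direction of the bias depends on that condition, and its size cannot be derived from the document. Under the stated assumptions with k from 2 to 4, a true 10% at month 3 would be seen as 8.5% to 6.1% with about 16% early leaving, or 7.3% to 3.1% with 25%. The baseline marks in both effects rows of Table 2 contradict the text and the order of baseline and randomisation; that part is certain but minor. The improvement is worth making because it is nearly free and reduces a plausible downward bias. The primary analysis is not affected.

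**What to change.** 1. State whether the withdraw questionnaire already asks exercise-arm participants about negative effects. If it does not, add the existing single item with its existing answer alternatives. In either case, list that form as a collection point in Secondary outcomes and Table 2.
2. Report the cumulative number of exercise-arm participants who ever report a negative effect, from quarterly and withdraw forms together. Give it over all randomised to that arm and over those who ever answered the item, with the number responding at each quarter beside the quarterly proportions.
3. Remove the baseline mark from both the positive-effects and the negative-effects rows of Table 2.

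The cost is one existing item on an existing online form, two corrected table rows and a few descriptive lines in the report. The withdraw form becomes slightly longer. Silent drop-outs who never complete it are still missed, which is why the responder numbers are needed. The change concerns data collection and reporting only, not the management of participants.
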